# Study Type

Double Blinded – randomized – prospective – investor – initiated clinical trail

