# Clinical Trial

Before patients will be included in this clinical trail, they must sign the consent form

and the acceptance of randomization. A Xerox of the patient consent form will be

given to the patient (participant).

The main list of randomization decides the treatment strategy and is oblique to be

included in the study. Patients which do not agreed with the randomization will be

excluded of the participance. The reason for withdrawal will be recorded (Question:

Which expectance did you established to the restoration material?)

According to indication, the cavity will be grained and an impression of the cavity

(Optosil) be undertaken. Ten questions regarding age, education, dental attendance,

oral hygiene, smoking etc. will be asked for the study record. The questions are part

of SHIP instrument (Study of Health in Pomerania, University of Greifswald).

The study box, handed out after the briefing lecture, contains blinded, numbered envelops, which contains only one single capsule. The use of this randomized material is binding. The capsule differs optically in the colour of the stamp. The colour code of the stamp shows, which coating (G-Coat LC or G-Coat Plus) has to be used in the last step. Is the necessity of an additional filling at the same volunteer indicated, the other study material will be used.

The filling will be placed according to manufacturers´ recommendations. To finish the

filling procedure, the surface has to be coated with G-Coat LC or G-Coat Plus (which

was used out of blinded, relabelled bottles by GC, Belgium) according to the random

list. Manufacturers´ recommendations and research methods will be trained before

(see above).

Regarding pseudonym procedure the patient will be registered by the next number in

the list and the envelope of randomization list will be opened to define the therapy

arm (G-Coat LC or G-Coat Plus). The bottles will be relabelled by “coat number A or

B”. The random list will tell the dentist to use bottle A or B. Only the project

management could identify the coat by the given numbers. So, neither the dentist nor

the participant will know in this blinded design which coat material was used.

*The materials get blinded and randomized by GC Europe. Only the information of the*

*expired date, colour (yellow, grey) is given to the participants.*

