# Examination

A member of the project team (calibrated examiner) will evaluate the fillings after the

first, second and the fifth year after placement. Criteria (see 16.1) out off the

publication of [name], R. et al. “Recommendations for conducting controlled clinical

Studies of dental restorative materials” (Clin Oral Invest (2007) 11: 5-33) and [name] et al_ FDI World Dental Federation: clinical criteria for the evaluation of direct and indirect restorations – update and clinica lexamples. Clin Oral Invest (2010) 14: 349–366, Appendix) will be used for examination.

The examiners will be calibrated once a year by external examiners. Additional the tool e-calib (www.e-calib.info) has to be used by the examiners for training purposes. The project team will organize the recall of the follow up in the local dental office in collaboration with the dentists.

To reduce costs the participating dentists will evaluate by their own for the baseline,

after the third and forth year. Replicas will be sent to the project team for evaluation.

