# Responsibilities

- LKP: [name]. [name]

OA [name]

- PI: OA [name] and calibrated examiner
  - Application for ethical board
  - Assiting statistical evaluation of data (done by [name]. math. [name])
  - Recruitment of local dental offices
  - Calibration of participating dentists
  - Contact person of participating dentists
  - SOPs (Study-Operating-Procedure)
  - Information form for participants
  - Consent form
  - Steering of baseline and Follow Ups 3,4
  - Follow Ups 1,2,5
  - Study files, documentation and archives
  - Randomization
  - Organisation of study groups per city
  - Records and communications
  - Final record
  - Publications
  - Cost control
- Examiner:
  - External Examiner (University Greifswald, University Marburg)
    - Local scheduling
    - Examiantion during Follow-up
    - Files, documentation
    - Report of adverse events to project group
    - Local data archive
    - Participation in study group
  - Dentist of local dental office
    - Files, documentation
    - Recruitment of participants
    - Local scheduling
    - Report of adverse events to project group
    - Local data archive
    - Participation in study group
- Statistics: project team ([name].-Math. [name])
  - Data Management
  - Data Safety
  - Statistical reports
  - Statistical calculations
- Medical documentalist
  - First Data entry (double entry N.N.)
  - Data management
  - Control of CRF
  - Feed back of Qeuries
- Data Safety and Monitoring Committtee ([name]. [name] and N.N.)
  - Data Management Control
  - Data Safety Control
  - Data Quality Control
  - Randomization Procedure Control
  - Veto: If quality reaches not the estimated level.
- Sponsor

o Event analysis

o Audit of files and archives

o Resources and financial support

o Organisation an arrangements of study groups and initial training

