## Randomization

- Randomized controlled clinical trial
- Control of randomization by project team and DSMC

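### The trial is called double blind, but nothing in the protocol keeps the examiners at years 1, 2 and 5, or the readers of the replicas, from the allocation

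*Protocol*

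**What the plan says.** - **Study Type** describes the trial as "Double Blinded – randomized – prospective – investor – initiated clinical trail".
- **Clinical Trial** has the coat bottles relabelled A and B, and a stamp colour on the capsule that shows which coat to use. It leaves the code with the project's management and begins its conclusion on blinding: "management could identify the coat by the given numbers. So, neither the dentist nor". The patient is the one other party that this conclusion names: "the participant will know in this blinded design which coat material was used". The same section also states: "The materials get blinded and randomized by GC Europe".
- **Clinical Trial**, on the filling record and impressions, has each impression labelled with the randomized envelope number and the patient's pseudonym.
- **Examination**: "A member of the project team (calibrated examiner) will evaluate the fillings after the" first, second and fifth year. Dentists grade at baseline and at years 3 and 4. Replicas go to the project team for evaluation, and the following subsection sends impressions there for scanning.
- **Follow Up** calls the examiner at years 1, 2 and 5 external.
- **Responsibilities** has a duty list headed "PI: OA [name] and calibrated examiner". It includes randomization, follow-ups 1, 2 and 5, and help with the statistical evaluation. A separate entry for external examiners, placed at Greifswald and Marburg universities, includes the follow-up examination and no randomization duty.
- **Randomization** (under the same part of the protocol): "Control of randomization by project team and DSMC".

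**The concern.** In a comparison of restorations the person whose blinding matters most is the one who decides whether a filling has failed. The protocol blinds the person who places the filling and the person who receives it, and leaves the assessor out. The duties it does assign bring allocation and assessment together.

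Most of the listed criteria are graded by judgement: surface lustre, marginal adaptation, occlusal contour and wear, tooth integrity. The Interpretation strategy counts failure by the published criteria, so borderline grades can become events. The stated hypothesis is that EQUIA survives better. An assessor who knows the arm could lean that way without intending to, at the three visits reserved for calibrated examiners, including the last. Analysis cannot remove such bias afterwards.

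**Working it through.** **1. The passages side by side**

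| Question | What the protocol gives |
|---|---|
| Who can decode the coat? | Project management (Clinical Trial) |
| Who is stated to be blind? | Dentist and participant only (Clinical Trial) |
| Who randomizes? | GC Europe (Clinical Trial); the PI and calibrated-examiner role (Responsibilities) |
| Who controls randomization? | Project team and DSMC (Randomization) |
| Who grades at years 1, 2 and 5? | A project-team member (Examination); an external examiner (Follow Up, Responsibilities) |
| Who measures replicas and scans? | Project team (Examination and its subsection on examination after application) |
| What is on the replica? | The randomized envelope number (Clinical Trial) |

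No entry keeps graders or readers from the code. Two features make the code easy to break. There are only two labels, so learning what one letter means decodes the whole list. A second filling in the same patient receives the other material, so knowing one arm reveals the other.

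**2. The plan's own figures**

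The plan gives no figure for assessment bias, so there is none to correct. Its hazards serve below as inputs, and they reproduce: exp(-0.0201 × 60) = 0.299 and exp(-0.0268 × 60) = 0.200, matching the 30% and 20% in the sample-size section. With 12 months' accrual, 60 months in total and a dropout hazard of 0.01 per month, the exponential test needs 439.3 to 441.7 fillings per arm, against the stated 440. This point does not change that number.

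**3. Illustration of size**

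Assumptions, not taken from the protocol: constant hazard, no dropout, each failure seen at the next yearly visit, 10% of one arm's failures passed as acceptable at years 1, 2 and 5 only, and correct grading at years 3 and 4.

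The share of five-year failures arising in year k is [S(12(k-1)) - S(12k)] / [1 - S(60)], with S(t) = exp(-λt). The sample-size section can be read with 30% and 20% as survival (λ = 0.0201, 0.0268) or with 20% and 30% as failure (λ = -ln 0.8/60 = 0.00372; -ln 0.7/60 = 0.00594). Both readings are shown.

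| λ per month | Years 1+2+5 | Years 1+2 | Year 5 |
|---|---|---|---|
| 0.0201 | 66.3% | 54.6% | 11.7% |
| 0.0268 | 68.8% | 59.3% | 9.5% |
| 0.00372 | 61.0% | 42.7% | 18.3% |
| 0.00594 | 61.6% | 44.3% | 17.3% |

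For example, at λ = 0.0201 year 5 gives (0.3811 - 0.2994) / 0.7006 = 0.117.

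A failure passed at year 1 or 2 is still present at year 3 at the latest, so it is delayed and not lost. Only failures passed at year 5 are lost.

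- Missed for good: 10% × (9.5% to 18.3%) = about 1.0% to 1.8% of the arm's five-year failures.
- Recorded late: 10% × (42.7% to 59.3%) = about 4.3% to 5.9%.

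As a share of all fillings the permanent loss is 10% × [S(48) - S(60)]: 0.82, 0.76, 0.37 and 0.52 percentage points in the order of the table.

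**4. What a shift does to the test**

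Take no true difference, 440 independent fillings per arm and a five-year proportion p of 25% or 75%. Then SE = √(2p(1-p)/440) = 0.0292. A shift x between arms gives a two-sided error of 1 - Φ(1.96 - x/SE) + Φ(-1.96 - x/SE).

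| Shift between arms | Actual error at nominal 5% |
|---|---|
| 1 point | 6.4% |
| 2 points | 10.5% |
| 3 points | 17.7% |
| 5 points | 40.2% |

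The permanent loss in step 3 is below one point, so on a fixed-time comparison its effect is small. Delay would also move the survival curves, which this table does not count.

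**The case against.** The strongest reply is that the link is inferred. Project management and project team are different terms, neither is defined, and the word only in the coat sentence reads as a restriction. Follow Up and Responsibilities describe an external examiner with no randomization duty. The list for the principal investigator also covers cost control, publications and the ethics application, so it may record overall responsibility and not who does each task. GC Europe prepares the blinded materials. Control of randomization need not mean access to the code. The follow-up record form has no field for the arm.

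Much of this stands. A reader might infer that the examiners are unblinded; the documents do not support that. But none of these passages states that graders or readers are blinded. External may mean only external to the dental practice. It conflicts with membership of the project team, and one of the two universities named is the study centre itself.

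Two further limits stand. The sample-size section defines loss as fracture or crack, which leaves less to judgement, although the Interpretation strategy uses the wider published criteria. Wear from matched scans is also less open to judgement than clinical grading, although the same team reads specimens that carry the envelope number. Failures seen between visits count from first occurrence, so the shares for years 1, 2 and 5 are upper figures.

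**Conclusion.** The point holds as a lack of protection, not as shown unblinding. The double-blind label is backed by a statement covering two parties. The assigned duties do not separate those who may know the allocation from those who grade and measure, and the passages on who randomizes and who examines disagree.

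The size is unknown. Under the assumed 10% misgrading at those visits only, about 1-2% of one arm's five-year failures are missed and about 4-6% are delayed. A reader might take 10% of the 61-69% share for years 1, 2 and 5 and infer a 6-7% fall in the failure count. That is wrong, because failures passed at year 1 or 2 are found by year 3 under the same assumption. Larger shifts would matter more, as the error table shows, but nothing in the protocol says how large a shift to expect.

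Two other inferences should not be drawn. The pseudonym keys concern the identity of offices and patients, not the arm. The sponsor's event-analysis duty is undefined, and that the manufacturer is the sponsor is itself an inference.

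**What to change.** - In Clinical Trial, Responsibilities and Randomization, name a holder who neither examines fillings nor measures replicas, and lodge the A/B code, the stamp-colour code and the randomization list there until database lock. The DSMC is one candidate, since it already has control of the randomization procedure.
- Remove randomization from the role that performs follow-ups 1, 2 and 5.
- Extend the blinding sentence to the calibrated examiners and to everyone who scores replicas or matches scans.
- Have replicas identified to readers by a number not linked to the randomization list.
- Reconcile who randomizes (GC Europe, or the principal investigator's role) and whether the examiners are external or members of the project team.

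The cost is mainly a reassignment of duties, plus a short procedure for custody and opening of the code and a relabelling step for replicas. If the DSMC is chosen, its membership must be settled first: one member had given only preliminary consent and the second is not yet named.

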# Calculation of the participants

The calculation of the numbers of participants were done with „nQuery 4.0“ software

by [name]. [name].

As aim (dependent variables) were used

- Loss of filling (dichotomy variable), defined as fracture or crack of the filling
- Abrasion of the occluded filled surfaces (scaled variable)
- Wear abrasion of the occlusal surface (scaled variable)

When the sample size in each group (Fuji IX and Equia) is 440, an exponential

maximum likelihood test of equality of survival curves with a p= 0.050 two-sided

significance level will have 90% power to detect the difference between a Group 1

exponential parameter, .1 of 20 % 0.0201 (corresponding to a proportion of 30% after

60 months) and a Group 2 exponential parameter, .2 of 0.0268 (corresponding to a

proportion of 20% after 60 months and a constant hazard ratio of

0.0201/0.0268=0.75) 30 %. This assumes an accrual period of 12 months, a

maximum follow-up time of 60 months (five years), and a common exponential

dropout rate of 1%.

The calculation is based on all incorporated units (fillings), e.g. all possible units

(fillings). The homogeneity of the participants will be guaranteed by the recruiting

phase, which will use the following selection criteria: Only one (at most two)

restoration for each side is calculated for each patient. The restoration will be limited

to posterior teeth (premolars and/or molars).

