After cure of the material, the shape of the filling has to get contoured (diamant 10-20 µm) and sealed according to the manufactured recommendation.

Conserving the shape of the filling for the study a replica will be done by one phase A-silicone (EXA fast Injection, GC Company) and impression tray with a setting time of prox. 360 sec. The impression methods will be trained during education of filling procedures. Interocclusal records (interponates) will be done with Green-bite apple (Co: Detax, Germany) during baseline and the follow-ups in central occlusion.

The participant gets a unique pseudonym in the dental office. The unique pseudonym

remains in the list of the dental office.

The filling protocol/record with the randomized envelope number, Probands ID, setting date, treated tooth/teeth and surface has to be filled out. The impression gets named with the randomized envelope number and Probands ID. After all fillings are set, the filling record has to be send to the University Greifswald.

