## Placement Protocol (Translation from german)

**Treatment Protocol Study Center Greifswald**

**[contact]**

After the placemt of the filling, please insert the Proband’s ID, the date of birth as well as the insertion date, the treated tooth / teeth and surfaces in the clinical record file.

| Envelope | Proband’s ID | Date of birth | Insertion date | Treated tooth/teeth |
| --- | --- | --- | --- | --- |
| ***Example*** | *# 3456* | *1.2.1965* | *21.6.2009* | *15mo, 16od* |
| **1** |  |  |  |  |
| **2** |  |  |  |  |
| **3** |  |  |  |  |
| **4** |  |  |  |  |
| **5** |  |  |  |  |
| **6** |  |  |  |  |
| **7** |  |  |  |  |
| **8** |  |  |  |  |

Dental office ID

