## Clinical Record File (CRF, Translation from German)

## Clinical Record File (CRF) Follow Up NU __     ____

| **Dental office ID _****______________** | |
| --- | --- |
| Date of Follow up: |  |
| Patient’s ID: | Pseudonym: |
| No:      Interponat: Replica: | |

| Treatment | 1 | 2 | 3 | 4 |
| --- | --- | --- | --- | --- |
| Tooth |  |  |  |  |
| Surface (S1, S2, S2mod) |  |  |  |  |
| A1  Surface lustre |  |  |  |  |
| B5  Fracture of material and retention |  |  |  |  |
| B6  Marginal adaptation |  |  |  |  |
| B7  Occlusal contour and wear |  |  |  |  |
| B8  Approximal anatomical form |  |  |  |  |
| B10  Patient’s view |  |  |  |  |
| C11  Postoperative (hyper-)sensitivity and tooth vitality |  |  |  |  |
| C12  Recurrence of caries (CAR), erosion, abfraction |  |  |  |  |
| C13  Tooth integrity |  |  |  |  |

See: [name] et al

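### The placement form, by its only worked example, invites several teeth on one envelope row with no material code per tooth, so the arm of each filling may be ambiguous in patients with several fillings

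*Protocol*

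**What the plan says.** All references are to the protocol.

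- **Clinical Trial, allocation.** Each numbered envelope holds a single capsule. The stamp colour on the capsule tells the dentist which coating to use, and the coating bottles are relabelled A or B. Only the project management can decode the labels. If the same patient needs a further filling, "the other study material will be used".
- **Clinical Trial, records.** "The filling protocol/record with the randomized envelope number, Probands ID, setting date, treated tooth/teeth and surface has to be filled out". For the replica: "The impression gets named with the randomized envelope number and Probands ID". Neither sentence mentions stamp colour or bottle letter, and the replica label has no tooth.
- **Appendix, Placement Protocol.** The dentist enters ID, birth date, insertion date and "the treated tooth / teeth and surfaces in the clinical record file". The form has eight rows numbered by envelope. The one example row carries one ID, one date and two teeth (15mo, 16od). Its envelope cell holds the word Example and no number.
- **Appendix, Clinical Record File.** The follow-up form has the patient ID in its header and up to four treatment columns. Each column has tooth, surface and graded criteria such as "Fracture of material and retention". The header has an undefined number field; no field is labelled as the envelope number.
- **Recruitment of patients (2nd Stage).** 1 to 3 fillings per patient (mean 2) and 3 to 8 patients per office (mean 5.5).
- **Calculation of the participants.** The unit of analysis is the filling. The plan sets 440 fillings per arm to reach 90% power at the two-sided 5% level, with exponential hazards of 0.0201 and 0.0268 per month.

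**The concern.** Dentist and patient are blind to material, so the arm of a filling must be derived from what the placement record holds. With one filling per envelope row this works: envelope number, then randomization list, then arm. With two teeth on one row it does not. Under the protocol's own allocation rule the two teeth carry different materials, but the row offers one envelope position and nothing to tell them apart.

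What is at stake is the main comparison. Survival and wear are contrasted by material, filling by filling. A tooth whose material was not captured at placement must be queried, dropped or guessed. Guessing pulls both contrasts towards no difference, and dropping costs events. An analysis plan cannot restore a link that the source record does not hold.

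**Working it through.** **1. The allocation rule against the form's example**

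| | Allocation rule (Clinical Trial) | Example row (Placement Protocol) |
|---|---|---|
| Envelope | one capsule each | one row position |
| Teeth | a second filling takes the other material | 15mo and 16od together |
| Material code by tooth | stamp colour, bottle A or B exist | no field |

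Read under the rule, 15 and 16 are one filling of each material. The row does not say which is which. Looking the row up in the randomization list would return one arm for both, which the rule shows to be wrong for one of them. The impression label (envelope number and ID, no tooth) does not separate them.

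**2. What the eight rows suggest**

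Expected fillings per office: 2 × 5.5 = 11; maximum 3 × 8 = 24. The maximum number of patients per office is 8. Eight rows match the patient maximum and would not hold the mean number of fillings at one per row on one sheet. This hints at a row per patient but does not prove it, since a second sheet is possible.

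**3. The planned power, reproduced**

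Inputs from Calculation of the participants: 440 fillings per arm, two-sided 5%, hazards λ₁ = 0.0201 and λ₂ = 0.0268 per month, accrual 12 months, maximum follow-up 60 months, dropout g = 1%. The time unit of the dropout is not stated; per month reproduces the plan.

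P(event) = λ/(λ+g) × [1 − (e^(−48(λ+g)) − e^(−60(λ+g))) / (12(λ+g))]

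- Group 1: 0.5356, so 440 × 0.5356 = 235.7 events.
- Group 2: 0.6276, so 440 × 0.6276 = 276.2 events. Total 511.8.
- SE of log HR = √(1/235.7 + 1/276.2) = 0.0887; |ln 0.75| / 0.0887 = 3.244; power = Φ(3.244 − 1.96) = 0.900.

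The stated 440 per arm is confirmed.

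**4. How many fillings could be exposed**

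Assume 1, 2 or 3 fillings per patient with mean exactly 2. The shares of patients with one and with three must then be equal; call each p, with p at most 0.5. The share of fillings in single-filling patients is p/2, so at most 25%. At least 75% of fillings are in patients with several. This is the pool in which the ambiguity can arise, not a predicted error rate.

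**5. Illustrative worst cases**

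*(a) Every patient on one row, all teeth credited to that row's arm, materials alternating.* Patients with two or three fillings then have one wrong filling each, so the wrong share is q = (1 − p)/2, between 25% and 50%. Mixing events and person-time between arms in proportion q:

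| q | Arises when | Observed HR | Power |
|---|---|---|---|
| 0 | one row per filling | 0.75 | 90% |
| 1/4 | half the patients with 1, half with 3 | 0.866 | 37% |
| 1/3 | 1, 2, 3 equally likely | 0.909 | 19% |
| 1/2 | all patients with 2 | 1.00 | no information |

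For q = 1/3: event probabilities are 2/3 × 0.5356 + 1/3 × 0.6276 = 0.5663 and 0.5970. Mean follow-up (event probability divided by hazard) is 26.65 and 23.42 months before mixing, 25.57 and 24.49 after. The rates are 0.02215 and 0.02437, HR 0.909. SE = 0.0884, z = 1.083, power = Φ(1.083 − 1.96) = 0.19.

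*(b) Every patient on one row, ambiguous fillings left unassigned.* At most 25% of 880 = 220 fillings remain, 110 per arm, with about 128 events. SE = 0.0887 × 2 = 0.1774; 0.2877 / 0.1774 = 1.622; power at most Φ(1.622 − 1.96) = 0.37.

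Both calculations treat fillings as independent and ignore clustering within patient and practice.

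**The case against.** The strongest reply is that the protocol nowhere orders several teeth onto one row. Rows are numbered by envelope and each envelope holds one capsule, so a second filling can open the next envelope and take its own row under the same ID. The case against the form rests on one specimen row, in a translated appendix, plus the wording that allows tooth or teeth. Dentists are trained under a procedure that is not shown. This stands as far as it goes: the form invites an ambiguous entry and does not prescribe it.

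A reader might go further than the documents in three ways.

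- **That the material can never be recovered.** Impressions carry the envelope number, entry forms are monitored in part, and queries are foreseen. An ambiguous row could be queried. None of this guarantees recovery: the impression label names no tooth, the record is sent in only once all fillings are set, and a row that copies the example would not look deficient.
- **That failures are being credited to the wrong arm.** This needs every patient with several fillings on one row and an analyst who gives all teeth on it the same arm despite the rule on the other material. The documents neither state nor imply such a rate.
- **That the follow-up form is defective for lack of an envelope number.** It is not. Patient ID with tooth and surface is an adequate key once each placement row holds one filling, and the undefined number field in the header may already serve.

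**Conclusion.** The point holds as a conflict between the placement form and the allocation rule. A form completed as its own example shows does not record which tooth is in which arm, and no other listed record settles it with certainty. For patients with several fillings entered this way, the arm is ambiguous and may be lost.

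Many fillings could be affected: with a mean of exactly 2 and a range of 1 to 3 per patient, at least 75% of fillings belong to patients with more than one. How many rows would be filled in like the example is unknown. The power figures, from 37% down to no information against the planned 90%, are worst cases. They assume that all such patients are entered on one row, that materials alternate, that dropout is 1% per month and that fillings are independent. They show why the link matters; they do not forecast the result. With one row per filling, nothing is lost and 440 per arm stands.

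**What to change.** 1. In the Clinical Trial section and on the Placement Protocol form, require one row per filling: its own envelope number, one tooth and its surfaces. Where the second material is assigned by rule without a further envelope, record the stamp colour or bottle letter for that tooth.
2. Replace the two-tooth example by two rows with the same ID.
3. Add the tooth to the label of each impression.
4. Optional cross-check: an envelope number or filling ID in each treatment column of the follow-up form.

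If forms have already been completed, list every row with more than one tooth and query the practice before the randomization list is opened.

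The cost is a form edit and one extra line per additional filling. Blinding is unaffected, since the codes are already visible to the dentist and decoded only by the project management. The sample size does not change.
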